## Abstract

**Introduction:**

Breast cancer (BC) is the primary cancer among women. The World Health Organization recommends a bilateral screening mammogram every 2 years for women aged 50 to 74 years. However, it has been shown that there is an absence of information about the benefits and risks of screening. Shared medical decision-making is important to ensure patients are involved in the decision process. Decision aids can facilitative this decision-making process. This article presents a protocol to evaluate the effect of a decision aid on participation rates in the French organized BC screening program.

**Methods and analysis:**

Design and setting. The design is a 2 arm randomized controlled study, performed in the Pays de la Loire region (French West Coast). Randomization will be based on general medicine practices (Primary Care).

**Participants:**

Women aged between 50 and 74 years, eligible for BC screening. In this region, there are 75000 women, and 2800 general practitioners eligible for recruitment.

**Intervention:**

In the « Decision aid for organized cancer screening » arm, the intervention will distribute invitation letters to eligible women combined with the provision of decision aid to these women and their general practitioners and an incentive to implement shared medical decision-making. In the « Standard organized cancer screening » arm, only the screening invitation will be sent to eligible women.

**Primary endpoint:**

BC screening participation rates will be assessed after an 18-month follow-up period.

**Statistical analysis:**

In this non-inferiority trial, the percentage of women who are up-to-date with their screening at 18 months after the intervention will be compared across arms using a generalized mixed linear model.

**Discussion:**

The research team expect to demonstrate that providing a better explanation of the benefits and risks of BC screening is not at odds with screening participation. The study results should help policy makers thinking about implementing shared medical decision-making within the framework of organized BC screening programs in the future.

**Ethics and dissemination:**

On 6 December 2021, the protocol received a favorable opinion from the French Committee for the Protection of Persons (2021-A01583-38). This study is registered with ClinicalTrials.gov, number NCT05607849. (Version 1, November 7, 2022; https://www.clinicaltrials.gov/ct2/show/NCT05607849). The study findings will be used for publication in peer-reviewed scientific journals and presentations in scientific meetings.

## Background

1

In 2020, breast cancer (BC) was the most commonly diagnosed cancer in women worldwide and was responsible for 1 in 6 cancer deaths (1). It was also the leading cancer in terms of incidence and mortality in French women (2).

International randomized trials have shown the effectiveness of BC screening using mammography, reporting a 15% to 20% decrease in specific mortality after 10 years of follow-up (3–8). To improve screening, the French authorities set up a national organized screening (OS) program in 2004 (9). The program targets women aged 50 to 74 years and follows World Health Organization (WHO) recommendations by inviting women at average risk for BC to have a bilateral mammogram every 2 years (10). It also provides reminders for women who have not spontaneously participated in screening within the recommended time intervals. All these invitations are sent by post. Current participation was 45.6% over the 2019-2020 period with a target of 65% (11).

Even within a framework for promoting screening, participation in screening remains an act of voluntary care and results from a health choice. In France, a citizen consultation highlighted dysfunctions in the current organization of screening and the subsequent consequences. These included a misunderstanding of the issues, and the absence of information about the benefits and risks of screening in the invitation letter sent every 2 years (12). The literature points out that the benefit/risk ratio of screening is difficult for a woman to predict from an individual perspective (3, 4, 13–16). Although participation in OS decreases mortality directly related to BC, it has significant disadvantages including false positive results, overdiagnosis and overtreatment which impact the patient’s quality of life (17). Health authorities recommend that these disadvantages are discussed in the invitation sent to these women, so that they have balanced and complete information, and can make an informed choice whether or not to participate in screening (12, 18).

Many authors have worked to improve information given to women and their involvement in the decision-making process. Shared decision-making is considered one of the fundamental approaches to improve health care quality (19, 20) Decision aids (DAs) can facilitate Shared Medical Decision-Making (SMDM). DAs should simply set out the best available evidence and the implications in terms of risks and benefits (21–23). Several DAs dealing with BC screening have been developed internationally (21, 23, 24). In 2018, the National Cancer Institute (INCa) funded the development of a DA specific to the French context as part of a call for research projects. The resulting DA was the “Discutons-mammo.fr” website, built in a collaborative and multi-professional way, and in accordance with international standards (25). The literature highlights that SMDM is best achieved if (i) women are informed about the existence of DAs and encouraged to discuss the OS with a healthcare professional (“coaching”) (26), (ii) health professionals are informed of the existence of DA, the different stages of the SMDM and the importance of their implementation (27). Finally, the use and dissemination of DAs requires evidence of their benefit, or at least evidence that DAs do not interfere with recommended care practices.

The primary objective of this study is to evaluate the impact sending a letter informing women of the existence of the DA “Discutons-mammo.fr” has on the BC screening participation rate in an organized setting, in routine practice and in the general population.

The secondary objectives are (i) to evaluate the predictive factors of using OS, and (ii) to measure the effectiveness of the intervention on SMDM implementation.

## Methods and analysis

2

### Design

2.1

The design is a non-inferiority, cluster, randomized controlled clinical trial with 2 parallel groups, performed in the Pays de la Loire region (West Coast of France) composed of 5 departments.

### Setting

2.2

In France, all patients over the age of 16 must follow a coordinated care pathway. General practitioners (GP) are at the center of this system. They coordinate access to care and specialists, are involved in screening and must be consulted as a priority. The GP system is based on a reciprocal choice: that of the patient and that of the GP.

The study is based on the regular GP/patient pair to measure the effect of the intervention. A cluster is defined as a group of GPs within the same primary practice address.

### Structure in charge of the organization of screening

2.3

OS management is entrusted to regional organizations in charge of cancer screening called CRCDC (“*Centre Régional de Coordination de Dépistage des Cancers*”). These organizations are in charge of collecting screening data for all women eligible for BC screening and follow-up cases with a positive or abnormal result. They collect information from health care providers (health insurance, pathology and cytology laboratories, hospital information systems, GPs, and cancer registries) involved in screening.

### Participants

2.4

Women aged between 50 and 74 years at the start of the study, who are eligible for BC screening, live in the Pays de la Loire region, and are registered with a participating GP will be eligible for inclusion in the study. Any women who are being followed-up for BC or an anomaly, have a medical or family history of BC, have refused or whose GP has refused to participate in the study, have participated in other studies on BC screening, or are under guardianship or curatorship will not be eligible for inclusion. Participating GPs will be the registered GPs for the included women practicing in the Pays de la Loire region. The inclusion and exclusion criteria for women and GPs are shown in **Table 1**. The list of eligible women will be extracted from the CRCDC. The association regular GP-eligible women will be realized by the health insurance system.

**Table 1 T1:** Inclusion and exclusion criteria for GPs and women.

	General practitioner	Women
Inclusion criteria	Specializing in General Medicine (excluding Special Practice Mode)	50 to 74 years old
	Working in Pays de la Loire	Residing in Pays de la Loire
	Having seen more than 100 different patients in the year prior to enrolment	Eligible for organized screening for the month in question
		Present on the patient list of a participating GP
		Affiliated to the health insurance system
Non-inclusion criteria	Refusing to participate in the study	Having a regular GP refusing to participate in the study
	Working in a Health Center	Affiliated with a health center
	Participating in other breast cancer screening studies	Participating in other breast cancer screening studies
		Under curatorship-tutorship
		Excluded from organized screening because they have a history of breast cancer
		Having ongoing follow-up (breast cancer or abnormality or medical surveillance or high-risk woman)

GP, General Practitioner.

### Randomization

2.5

GPs will be clustered within practices to avoid contamination bias stemming from shared tracking mechanisms and communication among GPs within a practice. As a result, two GPs working in a given practice will be assigned to the same study arm. The women will then be allocated to the same arm as their GP.

### Intervention and control procedures

2.6

One intervention arm and one control arm are planned.

In the “Decision aid for organized cancer screening” group (intervention arm), the intervention will combine sending letters to women and their GP. Women will receive their invitation to have a mammogram accompanied by a flyer mentioning the existence of the DA and encouraging them to consult their GP to make a shared decision. Physicians will receive a letter informing them of the correspondence their patients have received, the existence of the DA, a presentation of the different stages of SMDM and an incentive for their implementation.

In the “Standard organized cancer screening” group (control arm), the intervention will be limited to sending invitation letters, corresponding to the national standard (9).

### Participant blinding and informed consent

2.7

The GPs and women in the intervention and control arms will receive a regulatory letter by post informing them that they are participating in a study on screening (**Figure 1**). Opposition to participation in the study is possible in both arms for women and GPs.

**Figure 1 f1:**
[figure not shown]
Study design.

### Objectives, primary endpoint, and judgement criterion

2.8

#### Primary objective and primary endpoint

2.8.1

The main part of this study is to assess whether sending information to women and GPs mentioning the existence of DAs and encouraging SMDM implementation along with the screening information letter (intervention arm) affects participation rate in BC OS, compared to only sending the invitation letter to eligible women (control arm) (see **Supplementary Material 1**).

The primary outcome is the participation rate in BC OS, in each arm during the 18 months following the invitation being sent. This duration takes into account the waiting times observed to benefit from screening mammography (see **Supplementary Material 1**).

#### Secondary objectives and evaluation criteria

2.8.2

##### Assessing the predictive factors of the use of organized screening

2.8.2.1

The first secondary objective is to assess the predictive factors of OS use. Several studies have reported social inequalities in screening (28, 29). Suggested factors include increased age (30) and lower socio-economic status (31). Proxies of economic status are complementary health insurance status and French DEPrivation index of the place of residence. Therefore, as an associated secondary outcome, the study plans to collect the participation rate according to age and socio-economic level (beneficiaries of the Complementary Solidarity Health and municipality of residence according to the deprivation index).

In addition, the irregularity of women’s medical follow-up (32), the presence of a chronic pathology (33, 34) or psychiatric disorders (35, 36), and previous non-participation in screening (32) have also been reported as explanatory factors for non-participation in screening. Data will therefore also be collected over the 18-month period before and after the intervention to assess the health of participating women based on the Charlson Comorbidity Index (37) using the French health data collection system. Data will include: (i) the number of consultations and home visits to/by different healthcare professionals (GPs, midwives, gynecologists), and the number of journeys by taxi or medical transport, (ii) the prescription of certain reimbursed treatments and examinations performed (see **Supplementary Material 2**), (iii) participation in other cancer screenings.

##### Measure SMDM implementation and assess the level of decision-making conflict

2.8.2.2

The second secondary objective is to measure the effect of the intervention on SMDM implementation and quality, as part of an ancillary study. While the use of DAs is still marginal in occupational practices, the study should provide a better understanding of how such a tool is used and perceived when it is made available to healthcare professionals.

To assess the SMDM quality, a composite criterion will be used. The validated Shared Decision Making Questionnaire (SDM-Q-9) (38) will be used to evaluate SMDM implementation. The validated Decisional Conflict Scale (DCS) will be used to assess decision-making conflict (39). Intent to participate will be measured using a multiple-choice question. Knowledge about OS and women’s doubts, questions and concerns will be assessed and collected using a questionnaire created for the study. Secondary outcomes will be SDM-Q9 and DCS scores, intention to participate and level of knowledge. This will be measured 2 months after the intervention, in a sample of women from each study arm (see **Supplementary Material 1**).

### Collected data source

2.9

The CRCDC and the French Health Insurance System will collect the data needed to conduct the research in their databases. These data will be transferred to an open project space within the National Health Data System (NSDS) allowing their analysis. This data transfer will be carried out in accordance with the data protection regulations that govern personal data protection in the European Union. The Health Insurance data managers will pair the data collected from these databases at the patient level and proceed to data pseudonymization before analyses by the statistician.

### Statistical analysis

2.10

All data will be described globally and by randomization arm. The research is a non-inferiority clinical trial. The statistical unit is the woman eligible for screening. The materiality threshold will be set at 5% in a bilateral situation. Statistical analyses will be performed using R 3.6.0 software (R Foundation for Statistical Computing, Vienna, Austria. URL https://www.R-project.org/).

#### Main criterion

2.10.1

The percentage of women having undergone BC screening, 18 months after the intervention, will be compared between the arms using a generalized linear mixed model, to adjust the analysis for the random effect of the practice.

A two-sided 95% confidence interval of the difference in participation rates between the two arms will be calculated. The lower bound of this confidence interval will be compared to the non-inferiority margin. Non-inferiority will be demonstrated if the lower bound of the confidence interval is greater than the margin of non-inferiority defined at 2%, on the Intention to Treat (ITT) population and Per-Protocol population. If non-inferiority is demonstrated and if the participation rate in the intervention arm is higher than the participation rate in the control arm, the hypothesis will be verified with a superiority test (bilateral at 5%, according to the same model as that of the non-inferiority analysis) (40). If the test is significant, it will be concluded that the participation rate in the intervention arm is significantly higher than the participation rate in the control arm.

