#### Exploratory secondary analyses

2.10.2

Participation rates in exploratory subgroup analyses will be studied in the same manner as the primary endpoint. The same margin of non-inferiority will be used. There is no provision for alpha risk adjustment for these analyses. The different subgroups are: (i) women aged 50 to 59/60 to 69/70 to 74 years at baseline, (ii) beneficiaries/not beneficiaries of the Complementary Solidarity Health at baseline, (iii) women who consulted/did not consult at least one GP, gynecologist or midwife (during the follow-up period for women who did not have a bilateral mammogram during the 18 months, or from baseline until the date of the bilateral mammogram for women who had the screening) (iv) women residing in a municipality with a low deprivation index (per quintile of the deprivation index) (41).

Predictors of OS use will be assessed using a multivariate generalized mixed model fitted to the physician as a random effect, and as fixed effects: (i) the number of visits to the treating physician, GP, gynecologist, or midwife in the 18 months prior to enrolment, and from baseline to bilateral mammography or to the end of the follow-up period for women who did not have bilateral mammography, (ii) the woman’s age at baseline, (iii) the presence of a chronic condition measured *via* chronic drug use and testing, (iv) previous participation in OS.

A stepwise algorithm based on the Akaike information criterion (AIC) will be implemented to select variables that provide meaningful information independent of the main factors.

SMDM quality will be measured using the DCS and SDM-Q9 scales, responses to participation intent and knowledge of women about the OS. It will be compared between groups using a Student superiority test.

The care pathway of the women responding to the questionnaires will be studied and in particular the concordance between patients’ intention and effective participation in BC screening.

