#### Main study sample

2.11.1

Based on a participation rate in 2020 of 49% for the five participating departments (11) assuming a margin of non-inferiority of 2 points to demonstrate that participation is non-inferior in the intervention arm, and considering a power of 80% and a bilateral alpha risk of 5%, the number of women to be included is equal to 9,808 in each arm, being a total of 19,616 women.

There are 2,847 GPs in the five departments (42). Considering that GPs operate from 1,570 different practices (42) the number of women targeted per practice will be 48. With an average cluster size of 48 women and an intraclass coefficient of 5%, the number of subjects to be included to account for this cluster randomization must be multiplied by 3.35, or 65,647 women (32,824 per group).

The number of GPs included will be approximately 2,847 in the five departments. The recruitment potential is approximately 25,000 women per month (personal communication from the CRCDC). The inclusion will therefore be done over 3 consecutive months.

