**Evaluations:**										
Proportion of women aged 50 to 74 who had a screening mammogram 18 months after the procedure.										X
Participation rate 18 months after the intervention according to age, socio-economic level, medical follow-up, presence of a chronic pathology, psychiatric pathology, previous participation in screening.										X
SDM-Q9 and DCS scores 2 months after the start of the intervention.										X
Answers to the intention to participate questionnaire, answers to the knowledge questionnaire 2 months after the start of the intervention.										X

SDM-Q9, Shared Decision Making Questionnaire; DCS, Decisional Conflict Scale. X = realization of the stage.

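### The primary model is stated with a practice random effect only; pre-specifying previous screening participation as a baseline covariate would gain precision at almost no cost

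*Protocol article*

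**What the plan says.** All references are to the protocol article.

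- **Section 2.10.1 (Main criterion).** The percentage screened at 18 months "will be compared between the arms using a generalized linear mixed model, to adjust the analysis for the random effect of the practice". No fixed covariate is named. The follow-on superiority test uses the same model. The decision rests on a two-sided 95% CI for the difference in participation rates, in both the ITT and Per-Protocol populations.
- **Section 2.8.2.1.** Among the reported determinants, "previous non-participation in screening (32) have also been reported as explanatory factors for non-participation in screening". Age and socio-economic status are also given as suggested factors.
- **Section 2.10.2.** The secondary model for predictors of organized screening (OS) lists its fixed effects, including age at baseline and "iv) previous participation in OS".
- **Table 2.** The factors for the 18-month participation rate include "psychiatric pathology, previous participation in screening".
- **Section 2.3.** On the regional screening centres: "These organizations are in charge of collecting screening data for all women eligible for BC screening".
- **Section 2.11.1.** The sample size is "Based on a participation rate in 2020 of 49% for the five participating departments", "assuming a margin of non-inferiority of 2 points", with 80% power, a two-sided 5% alpha, 48 women per practice and an intraclass coefficient of 5%. It includes no covariate gain.

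**The concern.** Past attendance is a natural predictor of next attendance, and the article itself says so. The variable appears to sit already in the screening centre's records. The article lists covariates where it wants them, in the secondary model, so their absence from the primary model reads as a choice and not merely as condensed text.

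Precision matters here. The margin is only 2 points and the interval must clear it in two populations. A baseline covariate that explains part of the outcome variance narrows that interval without adding a woman to the trial. What is at stake is some power for the non-inferiority conclusion and for the superiority test that may follow.

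**Working it through.** **Inputs from the article.** Participation p = 0.49 in both arms, so p(1−p) = 0.2499. Margin 0.02. Two-sided alpha 5% (z = 1.96). Power 80% (z = 0.84). Cluster size m = 48, intraclass coefficient ρ = 0.05 (section 2.11.1). Planned inclusion about 75,000 (section 2.12).

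**Step 1: reproduce the plan's figures.**
- Per arm: n = 2 × 0.2499 × (1.960 + 0.842)² / 0.02² = 9,807.2, rounded up to 9,808; total 19,616. This matches.
- Design effect: 1 + 47 × 0.05 = 3.35. This matches.
- 19,616 × 3.35 = 65,714, against 65,647 stated (0.1% apart).

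**Step 2: power without covariates.** SE² = 2 × 0.2499 × 3.35 / (N/2), and power = Φ(0.02/SE − 1.96).
- N = 65,647: SE = 0.714 points, power 80.0%.
- N = 75,000: SE = 0.668 points, power 84.9%.

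**Step 3: assumed strength of the covariate.** The article gives none. Assume that half the women are previous participants and that participation differs by a gap g between them and the others. Then R² = 0.25 × g² / 0.2499:
- g = 30 points: 9.0%
- g = 40 points: 16.0%
- g = 50 points: 25.0%
- g = 60 points: 36.0%

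**Step 4: where the variance sits.** The design effect splits into a within-practice part, 1 − ρ = 0.95, and a between-practice part, mρ = 48 × 0.05 = 2.40. The between-practice part is 2.40/3.35 = 72% of the total. The gain therefore depends mainly on whether the covariate explains differences between practices, so two cases are needed:
- *Within only:* multiplier = 0.95 × (1 − R²) + 2.40.
- *Both parts in proportion:* multiplier = 3.35 × (1 − R²).

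**Step 5: power at 75,000 women, equal clusters.** The multiplier replaces 3.35 in Step 2.

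| Case | R² | Multiplier | SE (points) | CI half-width (points) | Power |
|---|---|---|---|---|---|
| Unadjusted | 0 | 3.350 | 0.668 | 1.31 | 84.9% |
| Within only | 9% | 3.265 | 0.660 | 1.29 | 85.8% |
| Within only | 36% | 3.008 | 0.633 | 1.24 | 88.5% |
| Both | 9% | 3.049 | 0.637 | 1.25 | 88.1% |
| Both | 36% | 2.144 | 0.535 | 1.05 | 96.3% |

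At the calculated 65,647 women, the same steps take 80.0% to 81.0–84.0% (within only) or 83.5–93.8% (both).

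These are normal approximations that treat the covariate as acting additively on the participation rate. They give the order of size and are not a forecast.

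**The case against.** The strongest reply is that nothing here is wrong. Practices are randomized, the model accounts for that clustering, and the comparison is valid without covariates. The sample size assumes none, and its power is reproduced. **This stands:** the point concerns efficiency only.

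A second reply is that a condensed article may leave the covariate list to the analysis plan. This carries some weight, since section 2.10.1 does not exclude covariates. It is not decisive, because section 2.10.2 does list fixed effects for the secondary model.

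A third reply concerns size. The upper range in Step 5 needs previous participation to explain between-practice variance in full proportion, and no figure in the article supports that. **This stands too.** A reader might turn R² of 9 to 36% into the equivalent of 10 to 56% more women, from 1/(1 − R²). That holds only in the favourable case; on within-practice variance alone, the gain is about 1 to 4 points of power.

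A reader might also fault the plan for a mismatch of scale, since a logit-link mixed model returns a conditional odds ratio while the margin is a difference in rates. The article states no link function and already calls for a CI of the difference. Standardization is a condition of the remedy proposed here, not a defect of the plan.

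**Conclusion.** The omission is in the text, and the direction of the gain is clear: power rises in every scenario computed. Its size is not documented. With an assumed R² of 9 to 36%, 75,000 women and equal practice sizes, power moves from 84.9% to between 85.8% and 88.5% at the cautious end, and to between 88.1% and 96.3% at the favourable end.

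It would be wrong to infer that the primary analysis is biased, or that the trial falls short of its own target. The unadjusted model delivers 80% at 65,647 women on the article's assumptions, and the planned inclusion is larger than that. The point is a worthwhile improvement and not the correction of an error.

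**What to change.** Before the database freeze at M30 (section 2.13):

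1. Pre-specify previous OS participation (yes, no, newly eligible) and age at baseline as fixed effects in the primary model, keeping the practice random effect. Complementary Solidarity Health status and deprivation quintile are optional additions; their benefit is not quantified here. Define the look-back for previous participation, which the article does not state.
2. Use baseline values only. The secondary predictor model also counts visits made after baseline; these must not enter the primary model.
3. Report the intervention-minus-control difference in participation rates with its two-sided 95% CI by marginal standardization that accounts for practice clustering, so that the result stays on the scale of the 2-point margin. Use the same model for the superiority test.
4. Keep the unadjusted model as a sensitivity analysis.

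The cost is wording and modest programming. New data are unlikely to be needed, since the secondary analysis already requires the main variable. Fixing the covariates now also rules out a data-driven choice later.

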### Justification of the non-inferiority margin

2.12

In a non-inferiority trial, the margin chosen must meet two criteria: (i) be less than the differences observed in the superiority trials already conducted, and (ii) be less than the Minimal Clinically Important Difference.

International evidence on whether the use of DAs changes participation in the OS is scarce, without clear direction. It may therefore result in an increase (44) or a decrease in participation rates (45). Recent studies do not show a change in participation rates when women are invited to participate in decision-making (43, 46, 47).

The non-inferiority margin was set at 2% in agreement with the BC OS medical experts at the CRCDC. This is the largest difference in clinically acceptable OS participation. The Cochrane literature review reports an average of 1 death averted per 2,000 women screened over 10 years (44), the observation of 10 healthy women who would not have been diagnosed if they had not participated in screening and who will be treated unnecessarily (44). Thus, of the 75,000 women who will be included in the study, and according to our participation hypotheses, a 2% decrease in participation in the intervention group would imply the non-screening of 750 women. No additional deaths from BC are expected following the procedure, but between 3 and 4 women will not be treated unnecessarily.

The trial will therefore be conclusive if the lower bound of the two-sided 95% confidence interval of the difference in participation between the randomization arms is greater than 2.

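### The non-inferiority rule in sections 2.10.1 and 2.12 compares the lower confidence bound with +2 instead of -2 percentage points and does not state the direction of the difference

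*Protocol article*

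**What the plan says.** Section 2.1 sets the type of trial: "The design is a non-inferiority, cluster, randomized controlled clinical trial with 2 parallel groups".

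Section 2.10.1 gives the estimate on which the decision rests: "A two-sided 95% confidence interval of the difference in participation rates between the two arms will be calculated". It does not say which arm is subtracted from which. The rule follows: "Non-inferiority will be demonstrated if the lower bound of the confidence interval is greater than the margin of non-inferiority defined at 2" per cent, to be met in both the intention-to-treat and the per-protocol populations. If it is met and the intervention arm has the higher rate, a two-sided 5% superiority test in the same model comes next.

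Section 2.12 closes with the same rule as a numerical comparison. The trial is conclusive if "the lower bound of the two-sided 95% confidence interval of the difference in participation between the randomization arms is greater than 2". Again there is no sign and no order of subtraction.

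Two other statements show what the margin is for. Section 2.11.1 sizes the trial "assuming a margin of non-inferiority of 2 points to demonstrate that participation is non-inferior in the intervention arm". Section 2.12 describes the consequence of reaching the limit: "a 2% decrease in participation in the intervention group would imply the non-screening of 750 women".

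**The concern.** A non-inferiority test on a beneficial outcome asks whether the new arm is worse by less than the margin. With the difference taken as intervention minus control, the lower bound must lie above minus the margin. Both statements of the rule put the threshold at plus 2.

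Neither order of subtraction turns the written rule into a non-inferiority test:

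- **Intervention minus control:** a lower bound above +2 demands proof that participation rises by more than 2 points. The superiority test that follows would then have nothing left to decide.
- **Control minus intervention:** a lower bound above +2 would show a loss of more than 2 points.

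This is the primary confirmatory criterion, and section 2.10.2 carries the same method and margin into the subgroup analyses. Section 3.1 expects average participation to stay about where it is. The literal rule has practically no chance of confirming that result. If the sign is settled only once results are known, a claim of non-inferiority would depart from the published rule.

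**Working it through.** **Inputs**

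- Section 2.11.1: control participation 49%, margin 2 points, power 80%, two-sided alpha 5%, 9,808 women per arm before clustering, mean cluster size 48, intraclass coefficient 0.05, 32,824 women per arm after inflation.
- Assumption: the intervention arm is also at 49% under the design alternative. The article does not say so, but the calculation reproduces the stated size.

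**1. Reproduce the stated size**

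n per arm = (1.96 + 0.8416)² × 2 × 0.49 × 0.51 / 0.02² = 9,807.2, rounded up to 9,808. This matches section 2.11.1.

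Design effect = 1 + (48 − 1) × 0.05 = 3.35. Then 19,616 × 3.35 = 65,714, against the stated 65,647 (0.1% apart, immaterial here).

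**2. Standard error at the planned size**

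Effective n per arm = 32,824 / 3.35 = 9,798.

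SE = √(2 × 0.49 × 0.51 / 9,798) = 0.00714, or 0.714 points.

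**3. Compare the two rules** (intervention minus control, normal approximation)

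- Written rule, lower bound > +2: the observed difference must exceed 2 + 1.96 × 0.714 = +3.4 points.
- Intended rule, lower bound > −2: the observed difference must exceed −2 + 1.96 × 0.714 = −0.6 points.

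| True difference (points) | Success, bound > +2 | Success, bound > −2 |
|---|---|---|
| −2 | practically 0 | 2.5% |
| 0 | about 0.000001 | 80.0% |
| +2 | 2.5% | above 99.9% |
| +3 | 29% | practically 100% |
| +4 | 80% | practically 100% |

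The zero row under the written rule is Φ(−3.4 / 0.714) = Φ(−4.76) ≈ 0.000001. Only the right-hand column gives both the stated 80% power at no difference and the one-sided 2.5% error at a 2-point loss. With 37,500 women per arm (half of the 75,000 in section 2.12) the written rule still needs an observed gain above about +3.3 points, and succeeds with probability about 0.0000004 at zero.

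**4. Check the unit**

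75,000 / 2 = 37,500 and 37,500 × 0.02 = 750, the figure in section 2.12. A relative 2% of 49% would be 0.98 points, or about 368 women. The margin is therefore absolute, in agreement with the 2 points of section 2.11.1.

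**The case against.** The strongest reply is that nobody would apply the rule literally. The design is called non-inferiority, section 2.12 speaks of a decrease in the intervention arm, and a superiority test comes afterwards. Quoting a margin as an unsigned size is common shorthand, and section 2.10.1 taken alone could be read that way. This largely stands: the intent is recoverable, and the one-in-a-million figure describes the rule as worded, not the likely fate of the trial. But section 2.12 writes the comparison out as a number, so shorthand does not explain both statements.

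A minus sign might have been lost in typesetting or conversion. The time point before 0 in Table 2 also shows none. That is not a credible explanation for two separate sections, one of which reads naturally without a sign.

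Four stronger readings are tempting and are not supported:

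- **The sample size proves the sign.** It does not. A superiority comparison of 49% with 51% using unpooled variances gives the same 9,807.2, because 0.49 × 0.51 is the variance in each arm. The wording of sections 2.11.1 and 2.12 establishes the direction.
- **The plan would declare success for a harmful intervention.** That needs control minus intervention, which no section states. A lower-bound criterion for a tolerated decrease points to intervention minus control. What stands is that the order should be written down.
- **The unit of the margin is unresolved.** The 750 women settle it as absolute points.
- **The superiority step is also wrong.** Nothing shows this. It is gated on non-inferiority and a higher observed rate, then tested at two-sided 5%.

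The point is not one left to a statistical analysis plan: the article states the rule and states it wrongly.

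**Conclusion.** Wrong as written. Sections 2.10.1 and 2.12 set the confirmatory threshold at +2 and leave the direction of the difference unstated, which contradicts the tolerated decrease in section 2.12, the sizing in section 2.11.1 and the superiority step in section 2.10.1 itself. Taken literally as intervention minus control, success has probability about 0.000001 at a true difference of 0, against the stated 80%, and reaches 80% only near +4 points. These figures assume 49% control participation, 32,824 women per arm, a design effect of 3.35 and a normal approximation.

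A reader might infer that the trial is underpowered or its design unsound. That does not follow. With the threshold at -2 points the planned size gives 80% power at no difference and 2.5% false success at a 2-point loss, as intended. The error lies in the stated rule and not in the sample size.

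**What to change.** In both section 2.10.1 and section 2.12, write that non-inferiority is concluded if the lower bound of the two-sided 95% confidence interval for participation in the intervention arm minus participation in the control arm is greater than -2 percentage points (absolute). Keep the requirement that this hold in both analysis populations, and leave the existing superiority step in section 2.10.1 unchanged. The subgroup analyses in section 2.10.2 take the corrected margin by reference.

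The cost is two sentences. Sample size, randomization and data collection do not change. The correction should be dated and on record before the analyses that section 2.13 schedules from month 30.
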